## ORVAC study design

ORVAC is a pragmatic, investigator-led, double-blind, randomised, placebo-controlled Bayesian adaptive clinical trial testing a third scheduled dose of Rotarix rotavirus vaccine (versus usual care) in Australian Indigenous infants to improve protection against clinically important gastroenteritis. It has the following key features:
Double-blind, randomised, placebo-controlled trial (neither the outcome observer nor participant’s caregivers know the treatment status);Non-fixed sample size up to 1000 participants (up to the first 250 with venous sampling) based on Bayesian stopping rules (minimum sample size of 70 for predicting futility);Fixed 1:1 parallel group enrolment into the active and control arm throughout the trial;Frequent interim analyses;Evaluation of intervention effects in the Darwin urban region compared to remote/very remote regions; andStudy participation is from randomisation until the end of follow-up at 36 months of age.

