### Secondary

The secondary objectives are exploratory and examine other aspects of effectiveness and immune response, see below and Table 1. Additionally, we will report on the safety and tolerability by examining the occurrence of intussusception potentially attributable to the intervention and the occurrence of serious adverse events.

**Table 1 Tab1:** Analysis methods for secondary outcomes

Endpoint	Overview
Time from randomisation to hospitalisation for which the primary coded reason for admission is presumed or confirmed acute gastroenteritis or acute diarrhoea illness between randomisation and age 36 months.	Summary of the median and inter-quartile range for each treatment arm. The analysis will follow the form of the analysis for the primary clinical endpoint. We will provide a competing risk analysis as discussed in the main text.
Time from randomisation to hospitalisation for which rotavirus confirmed diarrhoea illness occurs between randomisation and age 36 months.	Summary of the median and inter-quartile range for each treatment arm. The analysis will follow the form of the analysis for the primary clinical endpoint. We will provide a competing risk analysis as discussed in the main text.
Time from randomisation to rotavirus infection meeting the jurisdictional case definition between randomisation and age 36 months.	Summary of the median and inter-quartile range for each treatment arm. The analysis will follow the form of the analysis for the primary clinical endpoint. We will provide a competing risk analysis as discussed in the main text.
Change in anti-rotavirus IgA log titre between administration of intervention (RV1/placebo) and 28 to 55 days post dose.	We will adopt a robust linear regression analysis assuming the errors follow *t* distribution with between 3 and 7 degrees of freedom.
Frequency of intussusception fulfilling Brighton criteria within the first 28 days after administration of the third dose	Descriptive summary.
Frequency of serious adverse events between randomisation and age 36 months.	Descriptive summary.

Clinical outcomes comprise:

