Time from randomisation to hospitalisation for which the primary coded reason for admission is presumed or confirmed acute gastroenteritis or acute diarrhoea illness before age 36 months;Time from randomisation to hospitalisation for which the primary reason for admission is rotavirus-confirmed diarrhoea illness before age 36 months; andTime from randomisation to rotavirus infection (not necessarily requiring hospitalisation) that meets the jurisdictional case definition (for disease notification) before age 36 months.

Immunological outcomes comprise:
Change in anti-rotavirus IgA log titre between administration of the Rotarix or placebo dose and 28 to 55 days post dose.

Safety outcomes comprise:
The occurrence of intussusception fulfilling Brighton criteria [24] within the first 28 days after administration of the Rotarix or placebo dose; andSerious adverse events as defined by [25] between randomisation and age 36 months.

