#### Immunological co-primary outcome

The immunological outcome will be modelled using logistic regression including a covariate for treatment status (control arm coded as 0, treatment coded as 1). Denoting *y*_*i*_ as the seroconversion status, *π*_*i*_ as the probability of seroconversion and trt_*i*_ as an indicator variable for group membership for individual *i*, in the simplest case, we have:
1$$\begin{array}{*{20}l} y_{i} &\sim \text{Bin}(1, \pi_{i}) \end{array} $$

2$$\begin{array}{*{20}l} \text{logit}(\pi_{i}) &= \beta_{1} + \beta_{\text{trt}} \times \text{trt}_{i} \end{array} $$

However, we will also fit additional models that adjust for locality (urban versus remote), locality by treatment interaction, sex of participant, breast-feeding status in the 7 days prior to enrolment and community-specific indicators for gastroenteritis outbreaks.

We will use independent Student *t* distribution priors with location zero and scale 3 with 7 degrees of freedom that are recommended for general purposes [27, 28]. These priors imply
The parameters are as likely to be positive as they are to be negative;The intercept is consistent with baseline log-odds between − 10 and 10; andA unit change in any covariate would be unlikely to exceed an absolute change of 5 on the log-odds scale.

We note that these priors are similar to normal priors, which are also suitable for logistic regression, but the Student *t* has slightly heavier tails [28]. The Student *t* priors are considered weakly informative and produce stable, moderately regularised and robust estimates. When using the Student *t* priors, it is recommended that binary independent variables are shifted to have a mean of zero and differ by one and that continuous independent variables have a mean of zero and a standard deviation of 0.5 [27]. Therefore, we will adopt this transformation, which puts all the input variables onto the same scale.

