### Analyses of secondary outcomes

The secondary endpoints comprise time-to-event measures, discrete measures and continuous measures. Short descriptions of the methods to be used for each secondary outcome are detailed in Table 1.

As noted earlier, conventional statistical methods for the analysis of survival data assume that competing risks are absent. Given that the clinical outcomes (and adverse and serious adverse events) represent competing risks, the results from a sub-distributional hazard model will also be reported as has been recommended for RCTs [40, 41].

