### Interim analyses of co-primary outcomes

Bayesian adaptive trials rely on accumulating data and pre-specified decision rules to trigger adaptations. However, in order to ensure trial integrity, extensive simulation of the trial is required to investigate and quantify the operating characteristics such as the type I error rates, power and expected sample size under a range of hypothetical trial scenarios.

In this section, we outline the decision processes used for the interim analyses. Details on the simulations that were used to evaluate the operating characteristics of the trial are provided in a later section.

A simplified flow chart for the interim analyses and decision rules is presented in Fig. 1. The first interim analysis on the immunological endpoint will occur when 70 participants have full (baseline and follow-up) immunologic results. Further interim analyses occur after every subsequent 50 children or after every 3 months, whichever occurs sooner, unless there have been no new entrants. If there are no new blood samples and/or events, then we will defer the full analysis until the next scheduled interim. Analysis of the clinical endpoint will start when 200 children are enrolled in order that there are enough events to meaningfully undertake a time-to-event analysis.

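### The log IgA titre analysis in Table 1 names neither baseline titre nor the locality stratum as a covariate; stating both is a free, usually worthwhile gain in precision

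*SAP article*

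**What the plan says.** The Secondary section lists the outcome as "Change in anti-rotavirus IgA log titre between administration of the Rotarix or placebo dose and 28 to 55 days post dose", and Table 1 repeats it as "Change in anti-rotavirus IgA log titre between administration of intervention (RV1/placebo) and 28 to 55 days post dose". The method column reads "We will adopt a robust linear regression analysis assuming the errors follow" a t distribution, with the degrees of freedom put between 3 and 7. Nothing else about the model is given.

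Four other places bear on this:

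- Analyses of secondary outcomes: "Short descriptions of the methods to be used for each secondary outcome are detailed in Table 1". Table 1 is therefore meant to be brief.
- Secondary: "The secondary objectives are exploratory and examine other aspects of effectiveness and immune response".
- Immunological co-primary outcome: "we will also fit additional models that adjust for locality (urban versus remote), locality by treatment interaction, sex of participant", followed by breast-feeding status and outbreak indicators. Baseline titre is not in that list.
- Interim analyses of co-primary outcomes: the first analysis comes "when 70 participants have full (baseline and follow-up) immunologic results", so the baseline sample is part of the immunological data set.

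The Randomisation section states that allocation is stratified by regional versus remote residence. Venous sampling covers "up to the first 250 with venous sampling".

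**The concern.** A change score removes baseline by forcing its coefficient to 1. Entering baseline as a covariate lets the data estimate that coefficient. Unless the slope of follow-up on baseline really is 1, the forced value leaves avoidable noise in the treatment comparison.

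The titre row is also more exposed than its neighbours in Table 1. The three time-to-event rows borrow their form from the primary clinical analysis. The titre row borrows from nothing, so the covariates listed for the immunological co-primary do not carry over to it, and that list would not supply baseline titre in any case.

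Two things are at stake. The first is precision, in a comparison limited to at most 250 infants with blood samples. The second is an open choice: if the predictors are not fixed in advance, they can be chosen once results are known.

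**Working it through.** **Inputs from the SAP article.** Response: change in log titre. Model: linear regression with t errors, 3 to 7 df. Maximum sampled: 250. Allocation: 1:1.

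**Inputs the SAP does not give.** The correlation rho between baseline and follow-up log titre, and the two SDs. These are assumptions below. No sample size, power or precision figure is stated for this outcome, so there is no plan figure to reproduce.

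**Step 1: equal SDs (s at both times).**

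- Variance of the change: 2s²(1 − rho).
- Residual variance after adjusting for baseline: s²(1 − rho²).
- Ratio, adjusted over change: (1 + rho)/2. Variance saved: (1 − rho)/2. Reduction in standard error: 1 − √[(1 + rho)/2].

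| rho (assumed) | Ratio | Variance saved | SE reduction | 250 × ratio |
|---|---|---|---|---|
| 0.3 | 0.65 | 35% | 19% | about 162 |
| 0.5 | 0.75 | 25% | 13% | about 188 |
| 0.7 | 0.85 | 15% | 8% | about 212 |
| 0.9 | 0.95 | 5% | 2.5% | about 238 |

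The last column is the number of infants who, analysed with adjustment, give the same precision as 250 analysed by unadjusted change.

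**Step 2: unequal SDs.** Let k be the follow-up SD divided by the baseline SD. The variance saved is

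1 − k²(1 − rho²)/(1 + k² − 2k·rho) = (1 − k·rho)²/(1 + k² − 2k·rho).

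The numerator on the right is a square, so the saving is never negative. It is zero only when k·rho = 1, that is, when the slope of follow-up on baseline is 1.

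| k | rho 0.3 | rho 0.5 | rho 0.7 |
|---|---|---|---|
| 0.8 | 50% | 43% | 37% |
| 1.0 | 35% | 25% | 15% |
| 1.5 | 13% | 4% | 0.2% |

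Example for k = 1.5, rho = 0.5: (1 − 0.75)²/(1 + 2.25 − 1.5) = 0.0625/1.75 = 3.6%.

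**Step 3: the planned type of model.** The formulas above are for least squares. A simulation with t errors (5 df), a normal baseline, equal SDs, 125 infants per arm, a true effect of 0.3 and 1,500 replicates gave variance savings of 42%, 35% and 21% at rho 0.3, 0.5 and 0.7. Mean estimates were 0.29 to 0.30 with and without adjustment, so neither analysis was biased. This is one scenario and shows direction rather than an expected size.

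**Step 4: does the response need to change?** No. If change = follow-up − baseline and baseline is a covariate, switching the response from change to follow-up raises the baseline coefficient by exactly 1 and leaves the treatment coefficient as it was (apart from any trivial effect of a prior on the baseline coefficient). The outcome can keep its name.

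The gain from the locality term cannot be sized, because the SAP gives no figure for how log titre varies by locality.

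**The case against.** The strongest reply is that silence is not a decision. Table 1 neither includes nor excludes covariates, and does not even name the treatment term. Its entries are announced as brief, the article condenses a fuller plan, and a change outcome is compatible with baseline as a covariate (Step 4). This stands in part: a reader might infer that the trial chose an unadjusted analysis, and the text does not support that. What remains is that the row as written, with no cross-reference to another model, yields unadjusted change.

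A reader might also infer that 15% to 35% of precision is being lost. The document cannot support that as a fact. The figures are variance savings, they rest on assumed rho of 0.3 to 0.7 and on equal SDs, and the second table shows that they move a long way in both directions. Nor is it true that change scores lose precision whenever the correlation is below 1; there is no loss when the slope is 1.

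A third inference would be bias from regression to the mean. Under 1:1 randomisation the change analysis is unbiased. A chance baseline imbalance affects the particular sample obtained, not the validity of the method.

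Finally, the outcome is exploratory and enters no threshold in Table 2 and no stopping rule. Locality is not ignored either, since the Descriptive statistics section stratifies its summaries by it. Both points stand, and they limit the importance of the matter.

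**Conclusion.** The point holds as a minor one about precision and specification. Table 1 fixes a change score and an error distribution but does not say that baseline log titre or the locality stratum is in the model, although both are available for every infant with paired samples. In large samples, adding baseline cannot lose precision and will usually gain some. With equal SDs the variance saved is 35%, 25% or 15% at rho 0.3, 0.5 or 0.7. Across SD ratios of 0.8 to 1.5 and the same correlations it runs from about 50% down to about 0.2%. Every one of these figures rests on assumed correlations and SDs. No conclusion of the trial is put at risk.

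**What to change.** In the titre row of Table 1, state that the regression includes treatment, baseline log titre and locality stratum, with the same t errors, and that the adjusted difference will be back-transformed and reported as a geometric mean ratio with its 95% credible interval. Either change or follow-up log titre may be named as the response.

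The cost is one line, with no new data and no effect on sample size or on the interim rules. Because four interim analyses had been run by August 2020, with two trial statisticians unblinded, the line should be entered as a dated clarification, agreed by blinded investigators before the final immunological analysis.

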### Competing risks

Conventional statistical methods for survival analysis assume independent or noninformative censoring. However, the presence of competing risks violates the noninformative censoring assumption because the occurrence of one event influences the likelihood of a competing event from occurring [26]. While the co-primary time-to-event outcome defined here does not compete with any other event, the secondary clinical time-to-event outcomes and safety outcomes may represent competing risks. This is true even though the secondary clinical outcomes are not strictly mutually exclusive as it is sufficient that the occurrence of one event influences the probability of subsequent events of a different type for the competing risks context to be relevant.

Competing risks require special handling, and we return to this topic in a later section.

## Statistical analyses

ORVAC is a superiority trial that uses Bayesian methods for inference and decision-making. Unless otherwise noted, all parameter estimates will be reported as means or medians with 95% credible intervals.

### Descriptive statistics

Participant characteristics will be summarised by treatment group and stratified by locality. No formal statistical testing will be performed to compare groups at this stage. We will provide quantitative summaries of the participant data including:
Number of participants in ITT;Age at randomisation;Number of prior doses of Rotarix vaccination;Sex;Common comorbidities at randomisation;Breast feeding status;Anthropometric indices;Location of residence (urban versus remote);Proportion seropositive at baseline and seropositive/seroconverted at follow-up;Change in anti-rotavirus IgA between administration and second follow-up;Frequency of medical attendance events;Time to medical attendance events;Frequency of censoring;Frequency of intussusception;Frequency of adverse events; andOccurrence and timing of gastroenteritis outbreaks by community.

### Analysis of co-primary outcomes

We will assess both the immunological and clinical outcomes in a Bayesian framework with all model results reported. All models will be fit using Markov Chain Monte Carlo (MCMC).

#### Immunological co-primary outcome

The immunological outcome will be modelled using logistic regression including a covariate for treatment status (control arm coded as 0, treatment coded as 1). Denoting *y*_*i*_ as the seroconversion status, *π*_*i*_ as the probability of seroconversion and trt_*i*_ as an indicator variable for group membership for individual *i*, in the simplest case, we have:
1$$\begin{array}{*{20}l} y_{i} &\sim \text{Bin}(1, \pi_{i}) \end{array} $$

2$$\begin{array}{*{20}l} \text{logit}(\pi_{i}) &= \beta_{1} + \beta_{\text{trt}} \times \text{trt}_{i} \end{array} $$

However, we will also fit additional models that adjust for locality (urban versus remote), locality by treatment interaction, sex of participant, breast-feeding status in the 7 days prior to enrolment and community-specific indicators for gastroenteritis outbreaks.

We will use independent Student *t* distribution priors with location zero and scale 3 with 7 degrees of freedom that are recommended for general purposes [27, 28]. These priors imply
The parameters are as likely to be positive as they are to be negative;The intercept is consistent with baseline log-odds between − 10 and 10; andA unit change in any covariate would be unlikely to exceed an absolute change of 5 on the log-odds scale.

We note that these priors are similar to normal priors, which are also suitable for logistic regression, but the Student *t* has slightly heavier tails [28]. The Student *t* priors are considered weakly informative and produce stable, moderately regularised and robust estimates. When using the Student *t* priors, it is recommended that binary independent variables are shifted to have a mean of zero and differ by one and that continuous independent variables have a mean of zero and a standard deviation of 0.5 [27]. Therefore, we will adopt this transformation, which puts all the input variables onto the same scale.

We will calculate the probability that the log odds ratio (*β*_trt_) is greater than zero. If this probability exceeds 0.97, chosen by simulation to control the type I error, we will conclude a successful treatment effect of increased probability of seroconversion in the treatment arm. In notation, we conclude a treatment effect has been demonstrated if $\mathbb {P}(\beta _{\text {trt}} > 0)> 0.97$. We will report both absolute values of the proportion of participants that seroconverted in each arm and the treatment effect size as a difference in proportions and as odds ratios.

#### Clinical co-primary outcome

In time-to-event analyses, the Cox proportional hazards (PH) semi-parametric model [29] is commonly applied. This model does not require knowledge of the baseline hazard function, which is generally held as its chief advantage. However, parametric models (and some semi-parametric variants) have advantages such as greater efficiency, they provide smoothly estimated survival functions and are easy to fit [30–34]. For ORVAC, we will adopt a Weibull proportional hazard (PH) model with covariates introduced through the scale parameter [34]. We will undertake model checking using standard methods of posterior predictive checks, leave-one-out cross-validation and information criterion [34–37].

For the Weibull PH model, denoting the time to event as *t*_*i*_ for individual *i*, we have:
3$$\begin{array}{*{20}l} t_{i} &\sim \mathrm{W}(\lambda_{i}, a) \end{array} $$

4$$\begin{array}{*{20}l} h(t_{i}) &= \lambda^{*} a t_{i}^{a-1} \end{array} $$

where *h*(*t*_*i*_) is the hazard function. In the simplest case, we will set the scale parameter to *λ*^∗^=*λ*exp(*θ*_trt_×trt_*i*_), with the absence of an intercept being intentional [37], yielding a PH model with shape parameter *a* and with both *λ*>0 and *a* such that the hazard increases when *a*>1 and decreases when *a*<1. The corresponding survival function of the Weibull model is:
5$$\begin{array}{*{20}l} S(t_{i}) = \text{exp}(-\text{exp}(\theta_{trt} \times \text{trt}_{i}) \lambda t^{a}) \end{array} $$

from which it is implied that a plot of log(−log*S*(*t*_*i*_)) versus log(*t*_*i*_) will be approximately linear if the Weibull distributional assumption is reasonable. Furthermore, if analogous plots constructed for each treatment group yield parallel lines, then the proportional hazard assumption is valid. We will undertake model checking via the above heuristics and the usual Bayesian methods of posterior predictive checks and information criterion-based assessments. Finally, in cases where the PH assumption is violated, we will consider introducing time-dependent covariates or constructing an accelerated failure time (AFT) formulation as alternative strategies [38, 39].

For the shape parameter, *a*, we will adopt an exponential distribution prior with rate 0.7. This is consistent with values less than 10 and supports increasing and decreasing hazards with approximately equal probability. For the parameters in the linear predictor (the scale parameter and the hazard ratios), we will adopt independent normal priors (mean zero and standard deviation of 10). The normal priors are consistent with values on the log scale between − 15 and 15.

We will report the median time to event in each group and hazard ratios to quantify the treatment effect. In an analogous approach to that used in the immunological outcome, we will compute the probability that the parameter estimate for the treatment term is less than 0. If this probability exceeds 0.97 in the covariate-adjusted model, then we will conclude that a third scheduled Rotarix dose results in a treatment effect corresponding to a lower hazard of medical attendance in the treatment arm. In notation, we will conclude a treatment effect if $\mathbb {P}(\theta _{trt} < 0)> 0.97$.

We will use the methods as described above in the interim analyses including a single covariate for the treatment effect and using the predictive probability thresholds summarised in Table 2 for decision-making.

**Table 2 Tab2:** Probability thresholds for evaluating statistical triggers at interim and final analyses

Posterior/predictive	Decision	Threshold	Comment
Posterior	Win	0.97	Probability threshold to test that treatment difference is greater than zero
Predictive	Expected success	0.90	Proportion of successful trials must be greater than this threshold to claim expected success
Predictive	Futility	0.05	Proportion of successful trials must be in less than this threshold to claim futility
Predictive	Stop venous sampling	0.90	Proportion of successful trials must be greater than this threshold to stop venous sampling

In the final analyses for the clinical endpoint, if $\mathbb {P}(\theta _{trt} < 0) > 0.97$ in the adjusted model, we will claim trial success.

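### If one arm has no events, the normal(0, SD 10) prior on the log hazard ratio would determine the result for the two rotavirus-specific secondary outcomes

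*SAP article*

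**What the plan says.** Under Clinical co-primary outcome, the SAP article specifies a Weibull proportional hazards model with treatment coded 0/1 acting on the scale parameter, "with the absence of an intercept being intentional". For the shape, "we will adopt an exponential distribution prior with rate 0.7". For the scale parameter and the hazard ratios, "we will adopt independent normal priors (mean zero and standard deviation of 10"). The plan describes these normal priors so: "The normal priors are consistent with values on the log scale between" −15 and 15. On reporting it says "We will report the median time to event in each group and hazard ratios to quantify the treatment effect", and it also computes the posterior probability that the treatment coefficient is below zero. The opening of Statistical analyses adds 95% credible intervals for all parameter estimates.

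Table 1 lists the secondary outcomes. One is "Time from randomisation to hospitalisation for which rotavirus confirmed diarrhoea illness occurs between randomisation and age 36 months"; another is rotavirus infection meeting the jurisdictional case definition. For each, "The analysis will follow the form of the analysis for the primary clinical endpoint". No separate prior, minimum event count or sparse-data rule is given, although a competing-risk analysis is reported as well. The secondary objectives are described as exploratory.

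**The concern.** A prior with SD 10 on a log hazard ratio has little influence when both arms contribute events, because the likelihood then bounds the estimate on both sides. If one arm has none, the likelihood is flat in one direction and only the prior limits how far the estimate runs. This prior limits it very little: it puts about 65% of its mass on hazard ratios below 0.01 or above 100.

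The two rotavirus-specific outcomes are the ones where an empty arm is conceivable. They also bear most directly on the hypothesis in the Background, which concerns rotavirus gastroenteritis. A hazard ratio, interval and probability of benefit produced mainly by the prior tail could be published for them and read as data. The plan takes more care with the logistic model, where it chooses a Student t prior with scale 3 and 7 degrees of freedom because that regularises moderately.

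**Working it through.** **The plan's own figures.** For the exponential(0.7) shape prior, P(a<1) = 0.503 and P(a<10) = 0.999, so that description reproduces. For normal(0, 10), P(|θ|<15) = 0.866 and the central 95% range is ±19.6. The plan attaches no coverage level to its −15 to 15, so the statement is neither reproduced nor refuted. The plan gives no event count or rate for the rotavirus-specific outcomes.

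**Inputs from the plan.** Priors N(0, 10) on log λ and on θ; treatment coded 0/1; 1:1 allocation with at most 1000 participants, so 500 per arm; age at entry uniform on 6 to 12 months (mean 9), so mean follow-up is 36 − 9 = 27 months and exposure is 500 × 27 = 13,500 child-months per arm. **Assumption:** the event counts, which are hypothetical.

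**Model.** With shape 1, d0 placebo events, d1 vaccine events and exposure E per arm, the posterior is proportional to

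λ^(d0+d1) · exp(d1·θ) · exp(−λE − λe^θE) · N(log λ; 0, 10) · N(θ; 0, 10).

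This was integrated on a grid. Letting the shape vary under its stated prior, or using 150 or 350 per arm, leaves the results unchanged.

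**Hand check for 2 v 0.** With a flat prior on log λ, the likelihood for θ reduces to 1/(1+e^θ)², which tends to 1 as θ falls and to 0 as it rises. The posterior is then roughly the negative half of the prior. A half-normal with SD 10 has its median at −0.674 × 10 = −6.74, a hazard ratio of about 0.0012, and its far 2.5% point at about −22.4, a hazard ratio of about 2e-10. The grid result is of the same order and somewhat more extreme, because the likelihood also removes mass near zero.

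**Grid results, SD 10 (placebo v vaccine events).**

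| Events | P(HR<1) | Median HR | 95% CrI |
|---|---|---|---|
| 1 v 0 | 0.953 | 0.001 | 2e-10 to 2.1 |
| 2 v 0 | 0.985 | 0.0006 | 1e-10 to 0.67 |
| 3 v 0 | 0.994 | 0.0004 | 1e-10 to 0.39 |
| 0 v 2 | 0.039 | about 62 | about 0.7 to 7e5 |
| 10 v 5 | 0.91 | 0.47 | not needed |

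With no effect, two events both fall in the placebo arm with probability 0.5² = 0.25. The mirror split gives P(harm) = 1 − 0.039 = 0.96 with an interval that includes 1. The asymmetry comes from the 0/1 coding together with the separate prior on log λ.

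**Same 2 v 0 data, narrower priors on θ.** SD 5: P = 0.968, median HR 0.018. SD 2.5: P = 0.927, median HR 0.12, CrI 0.003 to 1.9. SD 1: P = 0.81, median HR 0.49, CrI 0.09 to 2.5.

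**Where the effect fades.** As a yardstick only, take how often P(HR<1) exceeds 0.97 with no true effect, using the conditional likelihood e^(d1·θ)/(1+e^θ)^(d0+d1) and a Poisson total.

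| Expected total events | 1 | 2 | 3 | 5 | 8 | 12 | 20 |
|---|---|---|---|---|---|---|---|
| SD 10 | 5.5% | 9.7% | 10.0% | 6.8% | 4.2% | 3.7% | 3.5% |
| SD 2.5 | 0.1% | 0.7% | 1.6% | 3.0% | 3.5% | 3.4% | 3.2% |

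**All-cause hospitalisation.** Trial population quotes median times of 15 to 40 months from birth. Treating the longest median, 40 months, as an exponential median and using 27 months of follow-up, the event probability is 1 − 2^(−27/40) = 0.374. That is about 112 events among 300 participants and 262 among 700, the range of expected sample sizes in the plan. This outcome is not sparse.

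**The case against.** The sparse case is hypothetical. The plan gives no rotavirus-confirmed rate, the Background describes a population with heavy rotavirus hospitalisation, and notified infection is broader than hospitalisation. This stands: the calculation shows what the prior does if an arm is empty, not that an arm will be empty.

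The carry-over of the prior is an inference. Table 1 speaks of the form of the analysis and does not mention priors. It remains the natural reading, because no other prior is given for these outcomes.

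A reader might infer that the 0.97 threshold would declare false wins on these outcomes. The documents do not support that. The threshold is stated for the co-primaries and the secondaries are exploratory, so the exceedance rates above are only a yardstick. A 2 v 0 result would also appear beside an extremely wide interval and a sub-distributional hazard model. Even so, that interval would exclude 1 on two events.

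A reader might also infer that chance splits produce near-certain harm as readily as near-certain benefit. Under the plan's own model they do not, as the 0 v 2 row shows.

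The Student t prior of the logistic model is no complete remedy. In the conditional calculation it gives P = 0.939 for 2 v 0 but 0.975 for 3 v 0. No figure in the plan singles out SD 2.5, which is a reasonable choice among several.

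**Conclusion.** The point holds within narrow limits. On the natural reading of Table 1, an empty arm in either rotavirus-specific outcome would yield a posterior shaped mainly by the prior tail. With 2 v 0 events that means P(HR<1) of about 0.985, a median hazard ratio of about 0.0006 and an interval of about 1e-10 to 0.67. This rests on the prior carrying over and on a hypothetical event count whose likelihood cannot be judged from the plan. The effect has largely gone by about 8 to 12 events in total.

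Three wider readings are not supported. The clinical co-primary and its interim decisions are not affected, since with many events this prior has little influence. All-cause hospitalisation is not affected on the plan's own medians. The −15 to 15 description of the prior is not shown to be wrong, because it claims no coverage level. This is a cheap improvement to two exploratory outcomes and does not threaten the trial's conclusions.

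**What to change.** In Table 1, for rotavirus-confirmed hospitalisation and notified rotavirus infection only, state a weakly informative prior on the log hazard ratio. Normal(0, SD 2.5) is one example: its central 95% range is exp(±1.96 × 2.5), or hazard ratios of about 0.007 to 134. Keep SD 10 as a sensitivity analysis and report event counts by arm beside each hazard ratio.

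The cost is one line of the plan and of code, plus slight shrinkage when events are few. With 8 placebo and 2 vaccine events the median hazard ratio becomes 0.26 instead of 0.22 (conditional likelihood). The priors for the co-primary and for all-cause hospitalisation can stay as they are.
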